### Sample size calculation

According to a survey of 11,000 physicians, on average, 53 patients are treated in medical practices per day [29]. Approximately 15 of these patients are health insured by AOK, which holds one third of the nationwide market share. According to epidemiological data, approximately 7 % of patients smoke 20 or more cigarettes per day. Assuming a participation rate of 50 %, physicians should be able to recruit around 10 patients for participation in the study per month. A meta-analysis by Stead and colleagues [7] demonstrates that among at-risk patients, the relative risk of being abstinent from smoking at follow-up is 1.65 for participants of intensive interventions, compared to participants of minimal interventions (with around 12 and 7 % cessation rates in the intervention and control groups, respectively). This value was transformed into a standardized mean difference (Cohen’s d) due to the metric scaling of our primary outcome. The expected small to moderate effect of Cohen’s d = 0.30 requires that data from 352 persons are available for sufficiently powered (β = 0.20) independent samples t-tests (α = 0.05). Accounting for the effect of clustering (intraclass correlation coefficient of 0.05) [30, 31]suggests that data from 34 medical practices with an average cluster size of 20 should be analyzed (340 patients per group, 680 in total). An estimated 15 % drop-out rate for medical practices means that 40 medical practices should be recruited. Due to an estimated 15 % of patients lost to follow-up, a total of 800 patients will be recruited for participation in the study. Assuming a 20 % participation rate in the smoking cessation program, 68 patients from the intervention group are expected to participate in the smoking cessation program. Figure 1 illustrates the expected flow of medical practices and patients through the study.

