## Background

In Germany, around 29 % of the adult population currently smoke, and 25 % of these smokers consume 20 cigarettes or more per day [1]. The negative health effects associated with regular tobacco consumption are well known: tobacco consumption is a risk factor for cancer, cardiovascular and respiratory diseases [2]. Furthermore, tobacco consumption complicates the treatment of many chronic diseases. Therefore, key elements in the treatment and secondary prevention of chronic obstructive pulmonary disease (COPD) [3] and coronary diseases are to avoid exposure to tobacco smoke [4]. Within the first year, abstinence from tobacco leads to an improvement in the lung function of COPD patients as measured by Forced Expiratory Volume in 1 second (FEV1). The progressive decrease in FEV1 can be stopped in the further course of treatment [5]. As a form of secondary prevention, smoking cessation reduces the risk of mortality associated with smoking-related diseases [6]. Moreover, a 50 % reduction in cardiovascular events is expected as a result of tobacco cessation [7]. Consequently, a number of different strategies to prevent tobacco consumption have been incorporated into prevention guidelines [8].

There are a number of different smoking cessation methods such as self-help measures, pharmacological aids, alternative treatments and individual or group counseling [9]. In contrast to pharmacological aids, certified smoking cessation programs are reimbursed in Germany. The smoking cessation program “Rauchfrei Programm” developed by the Institute for Therapy Research (IFT) in Munich and the German Federal Center for Health Education (Bundeszentrale für gesundheitliche Aufklärung) is most frequently offered by German health insurance companies [10]. The program consists of 3 to 7 weekly meetings with up to 12 participants and individual, telephone-based counseling [3]. The program is based on a cognitive-behavioral approach with the aim of creating problem awareness, motivating and achieving attitude as well as behavior change. Data from an evaluation (single group, pre-post-follow-up design) of the smoking cessation program in a routine setting with 1,319 participants demonstrate that the program is effective [11]. On average, participants smoked 20 cigarettes per day at the beginning of the program (*SD = 9)* and were heavily nicotine-dependent [11]. The abstinence rate was 61 %, and 32 % after 1 year [11].

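### The planning effect d = 0.30 for cigarettes per day is converted from a quit-rate ratio, and that conversion does not support the stated 80% power

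*Protocol article*

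**What the plan says.** The primary outcome is cigarettes smoked per day over 30 days, measured by the quantity-frequency index at 12 months (Outcome evaluation). Abstinence is a separate secondary outcome.

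The section Sample size calculation takes its effect from a meta-analysis of quitting: "the relative risk of being abstinent from smoking at follow-up is 1.65 for participants of intensive interventions", "with around 12 and 7 % cessation rates in the intervention and control groups, respectively". It continues: "This value was transformed into a standardized mean difference", the reason given being that the primary outcome is metric. The result is the planning effect: "Cohen’s d = 0.30 requires that data from 352 persons are available", for 80% power at α = 0.05 with an independent-samples t-test. An ICC of 0.05 and clusters of 20 bring this to 34 practices and 680 analysed patients. Allowance for drop-out gives 40 practices and 800 recruited.

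The section gives no expected difference in cigarettes per day, no SD, and no assumed reduction among patients who go on smoking. The only mean and SD for daily consumption are in the Background, for people entering the cessation programme: "On average, participants smoked 20 cigarettes per day at the beginning of the program", with SD 9.

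**The concern.** The usual conversions from an odds ratio to Cohen's d treat the binary event as a cut-point on a smooth underlying scale that treatment shifts as a whole. Daily cigarette consumption is not that scale. Quitters sit at exactly zero, and a difference in quit rates alone leaves everyone else where they were. A d that is valid for the latent scale can therefore be much larger than the d on which the t-test of mean consumption depends.

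At stake is how a non-significant primary result will be read. If the intervention raised quitting just as the cited evidence suggests and did nothing else, the primary test would probably miss it. A reader relying on the stated 80% power could then take the result as evidence that the intervention does not work.

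**Working it through.** **1. Reproducing the plan's figures.** For d = 0.30, two-sided α = 0.05 and 80% power, a t-test needs 175.4 per arm, rounded up to 176, or 352 in total. The design effect is 1 + (20 − 1) × 0.05 = 1.95. Then 352 × 1.95 = 686, or 34.3 practices, against the stated 680 and 34. Further, 680/0.85 = 800 and 34/0.85 = 40. With 340/1.95 = 174.4 effective patients per arm, power at d = 0.30 is 80%. The arithmetic from d onwards is sound, apart from slight rounding down.

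**2. Where 0.30 comes from.** 7% × 1.65 = 11.55%. The odds ratio is (0.1155/0.8845)/(0.07/0.93) = 1.735, and d = ln(1.735) × √3/π = 0.304. With the rounded rates, 12% against 7%, the same formula gives 0.328. A probit difference between 12% and 7% gives 0.301. The formula is thus an inference, but both candidates are latent-scale values and the objection applies to either.

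**3. What the quit difference does to mean consumption.** Let p be the quit rate, with quitters at zero, and let continuing smokers have mean m and SD s, the same in both arms. The arm mean is (1 − p)m and the arm variance is (1 − p)s² + p(1 − p)m². Assumed inputs are m = 20 and s = 9, from the Background.

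- Means: 0.93 × 20 = 18.6 (control) and 0.88 × 20 = 17.6 (intervention), a difference of 1.0 per day.
- Variances: 101.37 (control) and 113.52 (intervention), a pooled SD of 10.37.
- d = 1.0/10.37 = 0.096.
- Power at 174.4 effective patients per arm: about 15%.

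**4. Sensitivity to the assumed mean and SD (quitting only).**

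| Mean | SD | d | Power |
|---|---|---|---|
| 15 | 9 | 0.08 | 11% |
| 20 | 9 | 0.10 | 15% |
| 25 | 9 | 0.11 | 18% |
| 20 | 12 | 0.08 | 11% |
| 20 | 5 | 0.13 | 24% |
| any | 0 | 0.17 | 36% |

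The last row is a ceiling. If all continuing smokers smoke the same amount, m cancels and d = 0.05/√[(0.12 × 0.88 + 0.07 × 0.93)/2] = 0.05/0.292 = 0.171. Any spread among them only lowers d.

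**5. What d = 0.30 would require.** On SD 10.37 it is 0.30 × 10.37 = 3.1 cigarettes per day. Quitting supplies 1.0. The other 2.1 must come from the 88% of intervention patients who still smoke: (3.11 − 1.0)/0.88 = 2.4 fewer per day than continuing control smokers. (If the SD is recomputed to reflect that reduction, the figure is 2.3.)

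**6. Power by true difference, on SD 10.37 throughout.**

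| Difference per day | Power |
|---|---|
| 1.0 | 15% |
| 1.5 | 27% |
| 2.0 | 44% |
| 2.7 | 68% |
| 3.1 | 80% |

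**The case against.** The strongest reply is that d = 0.10 counts quitting only. The stated aim is to decrease tobacco consumption, the primary hypothesis is fewer cigarettes per day, and Table 2 labels it as smoke reduction. Patients who do not quit may cut down. As an illustration that is not in the document, suppose continuing intervention smokers smoked 10% less, 18 rather than 20 per day. The arm means would be 18.6 and 0.88 × 18 = 15.84, a difference of 2.76, with power of about 70% on SD 10.37. This stands. A reader might infer that the true effect is only a third of the planned one, or that a null result is likely. The document does not support either, because the cited relative risk is silent on reduction. But that same silence means the cited evidence does not yield 0.30.

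Second, the mean of 20 and SD of 9 are not planning inputs. They describe participants at the start of a cessation programme in a single-group evaluation. The trial also enrols patients with COPD or cardiovascular disease without the 20-per-day threshold, and only a fifth of the analysed intervention arm is expected to attend (0.20 × 340 = 68): "68 patients from the intervention group are expected to participate in the smoking cessation program". This also stands, so 0.10 is an illustration under labelled assumptions. The ceiling of 0.17 does not depend on those figures.

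Third, the conversion formula is inferred, as noted in the working.

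Fourth, abstinence is tested directly as a secondary outcome, so a null on cigarettes per day would not be the only evidence on quitting. That softens the consequence. It does not repair the power statement for the primary outcome.

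**Conclusion.** The point holds in this form: the quit-rate ratio does not justify d = 0.30 for mean cigarettes per day, so the stated 80% power has no support in the evidence cited. If quitting is the only thing that differs, at 12% against 7%, d is about 0.10 (0.08 to 0.13 over the means and SDs tried) and at most 0.17. Power is then about 15%, and at most 36%. This assumes that continuing smokers have the same distribution of consumption in both arms, 340 analysed patients per arm and a design effect of 1.95. The central value also rests on the borrowed mean of 20 and SD of 9.

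The 80% is unsupported, not proven unattainable. A reduction of about 2.4 per day among continuing smokers would deliver it, but the plan neither states nor justifies one. The fault lies in the effect-size input. The sample-size arithmetic that follows from it is correct to rounding.

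**What to change.** In Sample size calculation:

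- Delete the claim that d = 0.30 follows from the relative risk of 1.65.
- State the target as a between-arm difference in cigarettes per day on one SD that includes quitters at zero: about 3.1 per day at SD 10.4, with the mean and SD labelled as assumptions.
- Give power on that same SD: about 15% at 1.0, 27% at 1.5, 44% at 2.0, 68% at 2.7 and 80% at 3.1 per day. Quoting 2.7 per day at SD 9 for 80% would leave out the spread that the quitters add.
- State how much of the target must come from reduction among continuing smokers (about 2.4 per day on these assumptions), and the basis for expecting it.
- State that a null primary result does not exclude the 12% against 7% difference in quitting.

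The cost is a change of text and a less favourable power statement. The primary outcome, the number of practices and the number of patients stay as they are, so the change can be made with recruitment under way.

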### Recruitment and randomization

#### Recruitment of physicians

Letters of invitation to participate in the study will be sent to physicians situated in individual medical practices by AOK. Letters will be followed up via telephone by a research assistant from the University Medical Center Hamburg-Eppendorf, in case of no response. Physicians who agree to participate in the study via written consent will be randomly assigned to the intervention or control group (the intended allocation ratio is 1:1).

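### The 34 practices of 20 patients give about 77.5% power rather than 80% once the treatment effect is tested on the 32 degrees of freedom that the practices supply, and somewhat less if practice sizes vary

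*Protocol article*

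**What the plan says.** The Sample size calculation section of the protocol article starts from an expected d of 0.30, which "requires that data from 352 persons are available for sufficiently powered (β = 0.20) independent samples t-tests" at α = 0.05. It then allows for clustering with an "intraclass correlation coefficient of 0.05" and arrives at the analysed size: "data from 34 medical practices with an average cluster size of 20 should be analyzed", that is "340 patients per group, 680 in total".

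According to the Recruitment and randomization section, practices are the unit of allocation and "the intended allocation ratio is 1:1". The Data analysis section and Table 2 assign mixed models with physician and patient levels to the primary outcome, the quantity-frequency index. The sample size section mentions no allowance for the number of practices or for variation in practice size.

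**The concern.** The 80% power is attached to 352 independent patients and then carried over to 680 clustered patients by a design effect. That step assumes two things. First, it assumes that the test keeps the several hundred degrees of freedom of a patient-level t-test, although the treatment contrast is estimated between 34 practices. Second, it assumes that every practice contributes the same number of patients, although the protocol speaks only of an average of 20. Both assumptions make the stated power too favourable.

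If the trial ends without a significant difference, readers will take it as the result of an 80%-powered design. They should know that the planned numbers, achieved in full, give a little less than that.

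**Working it through.** **Inputs.** From the Sample size calculation section: d = 0.30 (SD 1), α = 0.05, β = 0.20, ICC = 0.05, 34 practices, mean size 20. From the Recruitment of physicians section: 1:1 allocation, so 17 practices per arm. Sidedness is not stated; two-sided is inferred because 352 reproduces only that way (a one-sided test would need about 278). The coefficient of variation (CV) of practice size and the baseline correlation are not in the documents and are assumed below.

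**1. The plan's own figure.** A two-sided t-test with 176 per arm and d = 0.30 has 80.1% power, so 352 is right.
- Design effect: 1 + (20 − 1) × 0.05 = 1.95.
- Inflated size: 352 × 1.95 = 686.4 patients; 686.4 / 20 = 34.3 practices. The plan states 34 and 680.
- Effective size per arm at 680: 340 / 1.95 = 174.4.
- Noncentrality: 0.30 × √(174.4 / 2) = 2.80.
- Power: 79.99% by normal approximation, 79.9% by t with 678 df.

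On the plan's own method, then, rounding down costs at most about 0.2 points.

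**2. Cluster degrees of freedom.** With 34 practices in two arms, df = 34 − 2 = 32. The two-sided critical value rises from 1.96 to 2.04. The noncentrality stays at 2.80.
- Power, noncentral t with 32 df: 77.5%.
- Effect detectable with 80% power: d = 0.31 (0.309).
- 36 practices of 20 (720 patients, 34 df): noncentrality 2.88, power 79.96%.

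**3. Unequal practice sizes (assumed CV).** For an efficiently weighted mixed model, the information relative to equal sizes is about 1 − CV² × λ(1 − λ), with λ = 20 × 0.05 / (20 × 0.05 + 0.95) = 0.513, so λ(1 − λ) = 0.25.

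| Assumed CV | Relative information | Power, 32 df |
|---|---|---|
| 0.2 | 0.990 | 77.1% |
| 0.4 | 0.960 | 75.8% |
| 0.6 | 0.910 | 73.6% |

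**4. Possible offset from baseline adjustment (assumed correlation).** If the mixed model adjusts for the t0 quantity-frequency index, and the correlation r with the 12-month value is the same within and between practices, the variance is multiplied by 1 − r². At r = 0.25 the noncentrality becomes 2.80 / √(1 − 0.0625) = 2.89. With one further df spent (31 df), power is 80.0% with equal sizes. At r = 0.4 it is 84%.

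**The case against.** The strongest reply is that the deficit is small beside the uncertainty of the inputs. The d of 0.30 was converted from a relative risk of abstinence, and the ICC is a round 0.05. At an ICC of 0.045 the same 34 practices of 20 give 79.5% on 32 df, and at 0.04 they give 81.6%. At d = 0.305 and ICC 0.05 the figure is 78.9%. This is fair and limits the weight of the point. It does not remove it, because the stated power is a claim about the inputs that the plan chose.

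Second, the article may leave the degrees-of-freedom method and the covariates to an analysis plan that is not shown. That silence is no fault. The point concerns the sample size calculation, which the article sets out with its inputs and result.

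Third, baseline adjustment could offset the loss. That also stands. The index is collected at t0, and a modest correlation would be enough. The article does not say whether the model adjusts for it, and the calculation claims no such gain.

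Two stronger readings are tempting, and the documents support neither:
- A reader might infer from 686.4 against 680 that the plan's own arithmetic already misses 80%. It does not: 680 gives 79.9 to 80.0% on that method.
- A reader might infer that power is as low as 70%. That figure needs a CV of 0.6, which the documents do not give, combined with the design effect 1 + ((1 + CV²) × 20 − 1) × 0.05 = 2.31. This design effect does not match an efficiently weighted mixed model, for which the same CV gives 73.6%. The word average shows only that sizes may vary, not by how much.

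**Conclusion.** The point holds at modest size. With all 34 practices and 680 patients analysed, d = 0.30, ICC 0.05, a two-sided 5% test and equal practice sizes, an unadjusted analysis has about 77.5% power rather than 80%. Equivalently, the design detects d of about 0.31. This shortfall of 2.5 points needs no input from outside the protocol except the inferred two-sided test.

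Any variation in practice size lowers the figure further. About 77% to 74% is a sensitivity range under an assumed CV of 0.2 to 0.6, not an estimate for this trial. Nor do the documents show that the final analysis must fall short of 80%, since adjustment for the baseline index could make up the difference. The calculation takes 34 practices of 20 as achieved and says nothing about attrition.

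**What to change.** - Restate the power of 34 practices of 20 as about 77.5% for an unadjusted analysis, or state the detectable effect as d = 0.31 at 80% power.
- Add the unequal-size sensitivity range (about 77% to 74% for a CV of 0.2 to 0.6), labelled as an assumption.
- Test the treatment effect in the mixed model with cluster-based degrees of freedom (Satterthwaite or Kenward-Roger), so that the analysis matches the restated calculation.
- Prespecify adjustment for the t0 quantity-frequency index. An assumed correlation of about 0.25 restores 80% with equal sizes and needs no more patients.

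If 80% is wanted without adjustment and with equal sizes, the analysed number is 36 × 20 = 720 patients. Spreading 687 patients over 36 practices (19.1 each) is not enough: the design effect is 1.90, the noncentrality 2.85 and power on 34 df about 79.0%.

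The cost is a slightly less favourable stated power. The t0 index is already part of the planned data collection.

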### Barriers to study completion

Possible barriers to the study’s implementation are seen primarily in the willingness of physicians to participate in research. However, this barrier will be addressed by actively following up on invitation letters with no response via telephone, engaging medical assistants in study processes and assuring adequate reimbursement in addition to training physicians individually. Despite these precautions drop-out is expected, specifically for medical practices that are assigned to the control group. However, the expected drop-out has been taken into account during sample size calculation. Another concern regarding the study’s implementation is seen in the low response rate of surveys. This concern will be addressed by conducting follow-up surveys via telephone because these have previously resulted in response rates of up to 85 % in studies to evaluate the program “Rauchfrei” by IFT [11].

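### 800 recruits cover only one of the two 15% losses the protocol assumes; if the losses compound, as the text most naturally reads, about 578 patients are analysed and power is about 77%, not 80%

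*Protocol article*

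**What the plan says.** All figures are in the protocol article, Sample size calculation, unless another section is named.

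- Unclustered requirement: "The expected small to moderate effect of Cohen’s d = 0.30 requires that data from 352 persons are available", with β = 0.20 and α = 0.05. Practices are allocated 1:1 (Recruitment of physicians).
- After allowing for an intraclass correlation of 0.05, "data from 34 medical practices with an average cluster size of 20 should be analyzed", which is 340 per group and 680 in total.
- Practice level: an estimated 15% "drop-out rate for medical practices means that 40 medical practices should be recruited".
- Patient level: an estimated 15% "of patients lost to follow-up, a total of 800 patients will be recruited for participation in the study".

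The Abstract places the 800 patients within the 40 practices. The section on barriers to study completion says that the expected drop-out was allowed for in the sample size. The visible text does not give the number of patients each practice should recruit, when practices are expected to leave, or whether patients of a practice that leaves are still followed. The expected flow is referred to Figure 1, which is not available here.

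**The concern.** Two losses are assumed at two levels, and each total is divided by 0.85 once: practices go from 34 to 40 and patients from 680 to 800. The levels are nested, however. Going from 34 to 40 practices at 20 patients each already takes 680 to 800, with nothing left over for patients lost within the practices that stay. Dividing 680 by 0.85 for patient loss gives the same 800, with nothing left over for whole practices that disappear. One number serves as the allowance for both.

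If the losses act one after the other, the analysed sample is smaller than the one for which 80% power was calculated. A null result would then be read as coming from a trial with a 20% type II error at d = 0.30, when the error would be a few points higher.

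**Working it through.** **Inputs from the protocol article.** d = 0.30; α = 0.05 (sidedness not stated; two-sided reproduces the stated total); power 80%; ICC 0.05; 34 practices × 20 analysed; 15% practice drop-out; 15% patient loss; 40 practices and 800 patients recruited.

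**1. Reproducing the plan's figures.**
- Two-sample t-test, two-sided 0.05, 80% power: 176 per arm, 352 in total. This matches.
- Design effect = 1 + (m − 1) × ICC = 1 + 19 × 0.05 = 1.95.
- 352 × 1.95 = 686.4, or 34.3 practices of 20. The plan uses 34 × 20 = 680; the difference is rounding.
- 34/0.85 = 40 practices and 680/0.85 = 800 patients. Both match.
- Also 40 × 20 = 800, the same total reached from the practice allowance alone.

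**2. Power at the stated target, 34 × 20.** Effective N = 680/1.95 = 348.7. Noncentrality = 0.30 × √(348.7/4) = 2.80. Power is 80.0% by the normal approximation, or 77.5% by a t reference with 34 − 2 = 32 degrees of freedom.

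**3. Both losses applied in turn to 40 × 20.**
- Practices: 40 × 0.85 = 34.
- Patients per remaining practice: 20 × 0.85 = 17.
- Analysed: 34 × 17 = 578 (= 800 × 0.85 × 0.85).
- Design effect = 1 + 16 × 0.05 = 1.80.
- Effective N = 578/1.80 = 321.1, against 352 required.
- Noncentrality = 0.30 × √(321.1/4) = 2.69. Power is 76.7% (normal) or 74.1% (t, 32 df).
- Detectable d at 80% power (normal) = 2.80 × 2/√321.1 = 0.313.

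Like for like, the loss is about 3 points: 80.0% to 76.7%, or 77.5% to 74.1%. Analysed patients fall by 15%, but effective N falls by only about 8%, because smaller clusters lower the design effect.

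**4. Recruitment that would absorb both losses.** 680/0.85² = 941.2, so about 942 patients, or about 23.5 in each of 40 practices.

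**5. Other ways the losses could combine.**

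| Reading | Analysed | Design effect | Effective N | Power (normal) |
|---|---|---|---|---|
| 20 recruited in each of 40 practices; lost practices give no data | 34 × 17 = 578 | 1.80 | 321 | 76.7% |
| 6 practices leave before recruiting; 800 come from 34 (800/34 = 23.5 each) | 34 × 20 = 680 | 1.95 | 349 | 80.0% |
| Practices leave after recruiting; their patients are still followed | 40 × 17 = 680 | 1.80 | 378 | 83.0% |

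**6. Baseline adjustment as a way back to 80%.** The cigarette measure is also collected at t0. If adjustment multiplies the outcome variance by 1 − r² at both levels (an assumption), effective N becomes 321.1/(1 − r²). With r = 0.30 this is 321.1/0.91 = 353, and power is 80.4% (normal). With r = 0.40 it is 321.1/0.84 = 382, and power is 81.2% (t, 32 df). The documents give no value for r.

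**The case against.** The strongest reply is that the text makes two inflations, one per level, and that 20 is the average cluster size to be analysed, not a recruitment quota. Reaching 578 requires 20 recruits in every one of 40 practices and the loss of every patient in a lost practice. Neither is stated.

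The alternatives also have some support. Drop-out is expected mainly in control practices, so it is tied to allocation, and patients are recruited after allocation. Practices could therefore leave before enrolling anyone. About 23.5 patients per remaining practice looks feasible at the assumed rate of around 10 per month. Follow-up is by telephone from the study centre, so a departing practice need not take its patients with it. Figure 1 might settle the matter.

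Part of this stands. A reader might infer that the plan's own assumptions leave 578 patients and that 80% power is definitely not delivered. The documents do not support so firm a statement.

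The alternatives are still the weaker readings. If patients of lost practices stay in the analysis, raising 34 practices to 40 has no purpose. Recruiting 23.5 per practice appears nowhere; 20 is the only per-practice figure, and the Abstract puts the 800 within the 40 practices. The expected 68 programme participants are 20% of 340, whereas 400 enrolled in the intervention arm would give 80. That is only suggestive, because 340 is also the analysed target per group.

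Three ways of enlarging the point should be resisted:
- Setting 74% (t) against 80% (normal) mixes two issues. The degrees-of-freedom penalty already applies at 34 × 20, where power is 77.5%.
- The step from 686 to 680 is rounding and leaves power at 80.0%.
- A reader might take 15% patient loss as a best case, because the section on barriers says of telephone surveys that "these have previously resulted in response rates of up to" 85%. The sample size section does not say that its 15% came from there.

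**Conclusion.** The point holds in qualified form. At patient level, 800 recruits cover one 15% loss, while the protocol assumes two. On the most natural reading the analysed sample is about 578 and power at d = 0.30 is about 77% instead of 80%. This assumes 20 recruits in each of 40 practices, no data from lost practices, ICC 0.05, equal cluster sizes and equal arms. The detectable effect at 80% power moves from 0.30 to about 0.31. The stated 680 and 80% can be rescued only by conditions that the visible text does not give.

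Severity is moderate. The shortfall is small and does not undermine the design, but the figure is one that readers of a null result will rely on, and it is cheap to put right.

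**What to change.** Keep 40 practices and 800 patients, and do one of the following in the sample size section and the expected-flow figure:

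1. State that the two losses compound: expected analysable sample about 578 (34 practices × 17), power about 77% for d = 0.30, detectable d about 0.31 at 80% power.
2. If 680 is what is meant, state the rule that makes it attainable: the recruitment target per practice (about 23.5 if only 34 practices recruit), when practices are expected to leave, and whether their patients are still followed.
3. Alternatively, state 80% power for a model adjusted for baseline consumption, with the assumed baseline–outcome correlation given and justified. About 0.3 suffices by the normal approximation and about 0.4 with t on 32 degrees of freedom.

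The cost is a few rewritten sentences and, under the first option, a slightly less favourable stated power. No extra enrolment is needed. Recruiting about 942 patients would also keep 680 after both losses, but a 3-point shortfall hardly warrants it.
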